### Assessing the older adults’ perception of mixed reality technology-driven health enhancing physical activity system’s usability and predictors of intention to participate in the program

#### Structural equation modeling

Structural Equation Modeling (SEM) through Partial Least Squares (PLS) will be employed to model the older adults’ perception of HT-HEPA’s system usability and predictors of intention to participate in the program. PLS-SEM is the most appropriate considering the number of older adult participants because of its power to precisely examine and estimate relationships among a set of variables (87, 88). This study will adopt the published guidelines for analyzing, interpreting, and reporting SEM outcomes (89) using the PLS Graph software package (90). For PLS-SEM, the measurement model’s evaluation is based on the reliability, construct, and discriminant validity of the measures associated with individual variables (89). Construct reliability assessment via composite reliability and Cronbach’s alpha (91) will measure the extent to which a set of items is consistent in what it intends to measure (90, 92). Convergent validity, on the other hand, is a measure of measurement instrument quality that can be assessed using two approaches: (a) evaluating the statistical significance (*p* < 0.05) of the item loadings associated with the construct and should be equal to or greater than 0.50 (90, 91) and (b) the use of average variance extracted (AVE) that quantifies the amount of variance that a construct captures from its items relative to the amount due to measurement error (93), greater than.50 (91, 94). The average variance extracted (AVE) can also be used to test if an instrument has discriminant validity, as evidenced by the AVE of each construct greater than its correlations with the other constructs (95).

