**Methods and analysis:**

An observational explanatory sequential mixed-method research design was conceptualized to examine the potential impact of a user-preferred mixed reality technology-driven health enhancing physical activity program directed toward purposively selected community-dwelling older adults in two senior centers in the Philippines. Quantitative components of the study will be done through a discreet choice experiment and a quasi-experimental study. A total of 128, or 64 older adults in each center, will be recruited via posters at community senior centers who will undergo additional screening or health records review by a certified gerontologist to ensure safety and proper fit. Treatments (live coaching with video-based exercise and mixed reality technology-driven exercise) will be assigned to each of the two senior center sites for the quasi-experiment. The participants from the experimental group shall be involved in the discreet choice experiment, modeling, and usability evaluations. Finally, a qualitative sample of participants (*n* = 6) as key informants shall be obtained from the experimental group using purposive selection.

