### Sample size

To identify the acceptable sample size, the difference in repeated measures between two independent groups using MANOVA with a power set at 0.80 with medium to high effect size at 0.05 alpha level was computed using R software. The estimated sample size is 128 or 64 participants per senior center group.

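### The discriminant-validity rule sets AVE against unsquared correlations, so it is stricter than the like-for-like criterion and can fail construct pairs that are distinct

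*Protocol article*

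**What the plan says.** The statistical methods for usability and intention to participate (Structural equation modeling) state that "Structural Equation Modeling (SEM) through Partial Least Squares (PLS) will be employed". The measurement model is then judged on reliability, convergent validity and discriminant validity.

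- AVE is described as a quantity that "quantifies the amount of variance that a construct captures from its items relative to the amount due to measurement error". For convergent validity it must exceed 0.50.
- Discriminant validity is then judged by the same AVE, "as evidenced by the AVE of each construct greater than its correlations with the other constructs".

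The article mentions neither a square root of AVE nor squared correlations, and it names no second discriminant criterion such as cross-loadings or a heterotrait-monotrait ratio. The Abstract places this work in one arm: "The participants from the experimental group shall be involved in the discreet choice experiment, modeling, and usability evaluations". With the planned numbers ("The estimated sample size is 128 or 64 participants per senior center group"), that means up to 64 people.

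**The concern.** The rule compares quantities on different scales. By the article's own description AVE is a proportion of variance: with standardised items it is the mean of the squared loadings. The variance that two constructs share is the square of their correlation, so AVE should be set against that square (the Fornell-Larcker comparison). Against the unsquared correlation, the hurdle is too high.

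At stake is the reported validity of the Phase 3 instruments. Quantitative aim 3 models acceptance, usability and behavioural intention together. These are neighbouring concepts, and moderate to fairly high correlations among them would be no surprise, although the protocol gives no figures. A pair in the affected range would be reported as not distinct on the strength of a mis-scaled rule. The article also offers itself in its Discussion as a reference for replication, so the rule may be copied.

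**Working it through.** **Inputs.** From the Structural equation modeling section: the rule AVE > r, and the convergent-validity floor AVE > 0.50. The rule is a criterion, so there is no computed figure of the plan to reproduce.

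**Scales.** For k standardised items with loadings λ, AVE = (λ₁² + … + λₖ²)/k. The variance shared by two constructs is r². The like-for-like rule is AVE > r², which is the same as √AVE > |r|.

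**Direction.** For 0 < AVE < 1, AVE < √AVE. With correlations taken in absolute value, any pair that passes AVE > |r| therefore also passes √AVE > |r|. The written rule can add failures but cannot add passes. The two rules disagree exactly when AVE ≤ |r| < √AVE, where AVE is the smaller of the pair's two values. In that range r² < AVE, so each construct shares more variance with its own items than with the other construct.

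**Size.** Correlation at which a pair starts to fail:

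| AVE | Rule as written | Like-for-like rule (√AVE) | Width of the affected range |
|---|---|---|---|
| 0.50 (plan's floor) | 0.500 | 0.707 | 0.207 |
| 0.60 | 0.600 | 0.775 | 0.175 |
| 0.70 | 0.700 | 0.837 | 0.137 |
| 0.80 | 0.800 | 0.894 | 0.094 |

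At the floor, the written rule rejects a pair from 0.50² = 25% shared variance; the like-for-like rule rejects it from 0.707² = 50%. Among the AVE values that the plan accepts, the gap is widest at the floor and narrows as AVE rises.

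**Illustration at n = 64.** A simulation used two constructs with four items each, equal loadings, and first-principal-component scores in place of PLS scores (3,000 samples per row). The number of items, the loadings and the true correlations are assumptions; none is in the protocol. Share of samples in which the pair fails:

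| Loading | True correlation | Rule as written | Like-for-like rule |
|---|---|---|---|
| 0.70 | 0.5 | 2.1% | 0.0% |
| 0.70 | 0.6 | 9.4% | 0.0% |
| 0.70 | 0.7 | 32.5% | 0.1% |
| 0.70 | 0.8 | 71.8% | 1.0% |
| 0.80 | 0.7 | 8.8% | 0.0% |
| 0.80 | 0.8 | 42.9% | 0.2% |

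The true correlation is not the one that the rule sees. With loadings of 0.70 the items correlate at 0.49, so the component AVE is about (1 + 3 × 0.49)/4 = 0.62. The score reliability is (4 × 0.49)/(1 + 3 × 0.49) = 0.79, so a true correlation of 0.7 appears as about 0.7 × 0.79 = 0.56, and one of 0.8 as about 0.63. This is why failures are a minority in the first case and a majority in the second.

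**The case against.** Three objections deserve an answer.

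*The sentence may be shorthand.* It says that AVE can be used in this way, cites a source, and sits in a section that adopts published SEM guidelines. An analyst may supply the missing square root. That is possible, and it lowers the certainty that the literal rule would be applied. But the article prints a rule, the printed rule is wrong, and nothing else in the article corrects it.

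*The consequences are easily overstated.* A reader might infer that constructs would be merged or dropped and that the reported predictors of intention would change. The documents do not support this. The methods section states no action after a failed check, and the Phase 3 design text speaks of a parsimonious model without tying it to AVE. Nor may one say that neighbouring constructs in general would fail: only pairs in the range above are affected, no correlations are given, and in the illustration many pairs pass under both rules. This objection stands in full.

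*The convergent-validity thresholds.* A reader might also see a contradiction between the loading threshold, which "should be equal to or greater than 0.50 (90, 91", and the AVE floor, since loadings all at 0.50 give AVE 0.25. There is none. The first is a minimum for each item and the second an average for the construct; the two are joined by *and*. A construct with all loadings at 0.50 meets the first and fails the second, and a single loading of 0.55 is compatible with AVE above 0.50 if other items load higher.

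**Conclusion.** The concern holds as an error in a stated criterion. Taken literally, the rule wrongly fails any pair with AVE ≤ |r| < √AVE: correlations from 0.50 to 0.707 at the plan's AVE floor, and from 0.60 to 0.775 at AVE 0.60. These limits follow from algebra alone; only the simulated failure rates rest on assumed items, loadings and correlations. The statement that there are no false passes takes correlations by absolute size.

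The scope is narrow. The rule bears on one measurement-model check in Phase 3, in the experimental group. It does not touch the repeated-measures comparison of physical, cognitive and quality-of-life outcomes in Phase 2. How many pairs would fall in the affected range, and what a failure would lead to, cannot be determined from the protocol.

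**What to change.** Reword the discriminant-validity sentence along these lines: *for every construct, the square root of its AVE must exceed the absolute value of its correlation with each other construct (equivalently, its AVE must exceed each squared correlation).*

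This changes one sentence and needs no extra data or participants. It should be made before the Phase 3 data are analysed. The convergent-validity thresholds need no change.

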### Understanding the older adult participants’ experiences during the mixed reality technology-driven health enhancing physical activities program

#### Thematic analysis

Interview texts will be transcribed, coded, and analyzed using MAXQDA^®^ Analytics Pro (VERBI Software, Germany). Member checking procedure (96) and reflective logs (97) will be adopted to ensure trustworthiness and reflexivity, respectively within the research team. Reflective notes or memos will be created to accumulate ideas, concepts, and connections with the generated quantitative data. Themes and/or subthemes shall be developed and reported using the COREQ guidelines (98). A code book will be created and maintained.

### Dissemination plans

The outcomes and changes in the study will be shared with the clients and stakeholders through post-study result dissemination and newsletter at the senior centers.

## Discussion

This protocol paper outlines the objectives, rationale, methods, and design for a multiple phase study that will examine the impact of a mixed reality-driven intervention through an exercise program directed toward community-dwelling older adults.

There has been increased research on older adult representations and studies focusing on technology interventions in the past decades (99). Although this upward trend is considered favorable in general, concerns related to ethical issues and the welfare of older adults participants are on the rise (100, 101), more so in aging studies involving technology interventions (42, 102). Older adults are essential to study subjects and clients in healthcare but are considered a vulnerable cohort in research studies.

As with other studies involving technologies, potential risks include loss of autonomy, privacy, data protection, safety, isolation prevention, and user overstressing. To minimize the risks, proper orientation will be held. The research team will undergo training and acquire good clinical practice certificate. Procedures will align with the currently accepted standards by the Philippine Department of Health, the research team will recruit social workers and healthcare providers to monitor the interventions and for potential health and wellness issues during the study. Reporting untoward events will comply with the current protocol and standards of the Philippine Health Research Ethics Board. Also, measurement error can be a potential challenge to the study and will be addressed by frequent recalibration and testing of instruments. Internet service interruptions needed to load exercise modules from the system storage might be an issue. This will be addressed by downloading the programs to the local server at the senior center sites.

This study protocol will provide an outstanding reference for future researchers for potential replication in other settings, timeline, and territories. It may also offer an outline of the necessary steps to ensure a robust but practical approach in technology studies in healthcare. The protocol supports the value of interdisciplinary and cross-disciplinary efforts and partnership in advancing the knowledge in the field of technology, health, and informatics. Outputs informing policies and standards are expected to be generated in this protocol for practice and research methods improvement.

## Ethics statement

The studies involving humans were approved by Johns Hopkins Medicine Institutional Research Board. The studies were conducted in accordance with the local legislation and institutional requirements. Written informed consent for participation in this study was provided by the participants. Written informed consent was obtained from the individual(s) for the publication of any potentially identifiable images or data included in this article.
